With an estimated 5% of its general population living with HCV, Pakistan has the second highest burden of this infection in the world [11]. A major scale-up of testing and treatment is needed if Pakistan is to eliminate HCV [12]. The current micro-elimination programme, led by Aga Khan University (AKU), is taking place in three Union Councils (UC) of Malir District in Karachi, Pakistan: UC-9 (Darsano Chano), UC-10 (Malh) and UC-11 (Murad Memon). This micro-elimination programme brings HCV screening, diagnostic and treatment services to people’s doorsteps and aimed to test around 30,000 people, as described previously [13]. However, the current programme has not been able to screen the entirety of the planned coverage area due to an estimated 39% of household members being absent when AKU staff made their field visits. The present study will assess whether secondary distribution of HCV self-testing can increase testing uptake among individuals who were unavailable during the visit by testing campaign staff. In the context of HIV, the secondary distribution of HIV self-tests during door-to-door testing campaigns substantially increased testing coverage (by 21%) among absent individuals or those who declined to participate [14]. The current study will be the first to explore this mode of delivery of self-testing for HCV.

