### Outcomes

The primary outcome is to assess whether the proportion of participants who report completing HCV antibody testing in the intervention group is greater than that of the participants in the control group by a margin of 20%.

The secondary outcome measures are as follows.The number and estimate of the proportion of HCV antibody-positive individuals made aware of their antibody status in the intervention versus the control groupThe number and estimate of the proportion of HCV antibody-positive individuals who are referred for and complete HCV RNA confirmatory testing in the intervention versus the control groupThe number and estimate of the proportion of HCV RNA-positive individuals who begin treatment in the intervention versus the control groupThe cost per test completed and the cost per person diagnosed (serology, RNA) in the intervention versus the control groupAn analysis of the knowledge, attitudes and practice survey responses will be conducted, using proportions and means

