### Participant timeline

#### Sample size

A minimum of 2,000 participants who meet the inclusion criteria will be enrolled in the study. There will be up to 20 clusters, each comprising up to 150 to 200 households: 5 intervention clusters each in rural and peri-urban areas and 5 control clusters each in rural and peri-urban areas. The study is powered to detect at least a 20% between-group difference in HCV antibody self-testing, based on 80% statistical power and an alpha level of 0.05.

The survey of participants’ perceptions in relation to testing will include face-to-face interviews with 60 participants from each of the intervention and control groups. This is guided by empirical thinking, considering the feasibility with regards to the time and staff required to conduct the in-person interviews. The aim of these interviews is to further expand our understanding of preferences around HCV self-testing; there is no intention to set specific targets for measurement.

For the primary objective, the null hypothesis is that there is no significant difference in the proportion of individuals reporting HCV test results in the intervention versus control groups. The alternative hypothesis is that home delivery of HCV self-tests will significantly increase the proportion of individuals reporting HCV test results.

The study is not powered to detect significant differences in the secondary objectives. However, similar to the primary objective, the null hypothesis would be no significant difference between the intervention versus control groups. The alternative hypothesis would that home delivery of HCV self-tests will result in significantly higher numbers of HCV-infected individuals being diagnosed, linked to care and treated, making it a cost-effective approach to HCV case finding and elimination.

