Test result and consequence 1		Positive and referred to further testing	Positive and not referred to further testing	negative	No result		
Test result and consequence 2		Positive and treated	Positive and not treated				
Study arm	Intervention	a	b	c	d	e	(a + b + c + d + e)
	Control	f	g	h	i	j	(f + g + h + i + j)
Total		(a + b + c + e + f + g + h + i)				(e + j)	total

The consequences (referred, treated) will be analysed independently of each other

The number and estimate of the proportion of participants who report completing HCV antibody testing in the intervention group will be calculated as:$$\mathrm{pfo},\mathrm{I }= (\mathrm{a}+\mathrm{b}+\mathrm{c}+\mathrm{d})/(\mathrm{a}+\mathrm{b}+\mathrm{c}+\mathrm{d}+\mathrm{e})$$$$\mathrm{pfo},\mathrm{C }= (\mathrm{f}+\mathrm{g}+\mathrm{h}+\mathrm{i})/(\mathrm{f}+\mathrm{g}+\mathrm{h}+\mathrm{i}+\mathrm{j})$$

The absolute and relative proportions will be calculated separately by arm (all arms) and reported with their two-sided 95% Wilson score confidence interval.

The difference pfo,I—pfo,C will be assessed using a one-sided test with a margin of 20%, by applying the following hypothesis:$$\mathrm{H}0:\mathrm{ pfo},\mathrm{I }-\mathrm{ pfo},\mathrm{C }\le 20\mathrm{\%}$$$$\mathrm{HA}:\mathrm{ pfo},\mathrm{I }-\mathrm{ pfo},\mathrm{C }> 20\mathrm{\%}$$

The difference of the proportions in the intervention and control arms will be reported, together with its confidence interval (see below) and the *p*-value related to the null hypothesis mentioned above.

The alpha level for the analysis will be set at 0.025 (1 one-sided test with an alpha level of 0.025).

The difference and its confidence interval will be estimated using a generalised binary mixed logit model with “cluster pair” as a random effect and “group” as a fixed effect (e.g. using the R function “lmer”). The two-sided 95% asymptotic confidence interval will be used to derive the one-sided lower 97.5% confidence limit, which will be used for interpretation. In addition, the odds ratio and its confidence interval will be reported.

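### The article states two different primary nulls, and its 80% power at a 20-point difference is wrong for the test with the 20-point margin, where that power is 2.5%

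*Protocol article*

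**What the plan says.** The 20% figure plays two roles in the protocol article.

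- **Outcomes.** The primary outcome asks whether the intervention proportion "is greater than that of the participants in the control group by a margin of 20" per cent. Endpoint 1.2 in Table 2 repeats the margin.
- **Statistical methods.** The difference "will be assessed using a one-sided test with a margin of 20%, by applying the following hypothesis": H0: pI − pC ≤ 20%, HA: pI − pC > 20%. Alpha is 0.025 one-sided. The reported p-value refers to this null, and the lower 97.5% confidence limit is used for interpretation.
- **Sample size.** "A minimum of 2,000 participants who meet the inclusion criteria will be enrolled in the study", in up to 20 clusters. The target is worded as follows: "The study is powered to detect at least a 20% between-group difference in HCV antibody self-testing". The section sets power at 80% and alpha at 0.05, without saying whether the test is one-sided or two-sided. For the primary objective, "the null hypothesis is that there is no significant difference in the proportion of individuals reporting HCV test results" between the groups.

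The Design section calls this a superiority trial and mentions no margin. The study aim speaks of the impact of self-testing on testing rates. No section assumes a true difference above 20 points.

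**The concern.** A margin in the null hypothesis and a difference to be detected are separate quantities. Power against a margin must be computed at a true effect beyond that margin. Here the same 20% is both the null boundary in the analysis and the target difference in the power statement, while the Sample size section puts the null at zero.

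The success criterion for the primary outcome is at stake. A true gain of 20 points would very probably meet the criterion in the Sample size section and would almost always miss the one in Statistical methods. If both remain in print, the choice could be made after the results are known, and the type I error claim would then be lost.

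**Working it through.** **Inputs from the article.** N = 2,000 (minimum); allocation 1:1, so about 1,000 per arm; up to 20 clusters, so 10 per arm and about 100 participants per cluster; difference 20%, read as percentage points because the hypotheses are on that scale; 80% power with alpha 0.05 (Sample size); one-sided alpha 0.025 (Statistical methods). The two alphas agree only if 0.05 is two-sided.

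**Assumed, because the article gives neither:** control uptake pC and ICC.

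**Step 1: the stated 80%, against H0: difference = 0.** Under individual randomisation, detecting pC versus pC + 0.20 at two-sided 0.05 and 80% power needs 49 to 97 per arm for pC from 5% to 75% (97 at pC = 40%). At pC = 40%, 1,000 per arm allows a design effect of 1000/97 = 10.3, and so an ICC of (10.3 − 1)/99 = 0.094. At pC = 5% or 75% it allows 1000/49 = 20.4, an ICC of 0.196. The 80% is therefore attainable as a test against zero if the ICC is about 0.09 to 0.20. It cannot be confirmed without the missing inputs.

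**Step 2: the test with the margin, at a true 20 points.**

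SE = √{[pC(1 − pC) + pI(1 − pI)]/1000 × (1 + 99·ICC)}

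Power = Φ((d − 0.20)/SE − 1.96)

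At d = 0.20 the first term is zero for every SE, so power = Φ(−1.96) = 2.5%. Neither N, ICC nor pC matters. If 0.05 were meant as one-sided, the figure would be 5%.

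**Step 3: simulation check.** 20,000 trials were simulated at each ICC, with 10 + 10 clusters of 100, pC = 40% and pI = 60%. The test was a simple cluster-level t-test on 9 df, not the planned mixed logit model.

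| ICC | rejects H0: difference ≤ 20 points | rejects H0: difference ≤ 0 |
|---|---|---|
| 0 | 2.5% | 100% |
| 0.02 | 2.6% | 99.6% |
| 0.05 | 2.9% | 90.7% |

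**Step 4: power at larger true differences.** The formula is that of step 2, with pC from 10% to 50%.

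| ICC | power at a true 25 points, pC = 40% | true difference for 80% power |
|---|---|---|
| 0 | 64% | about 25–26 points |
| 0.02 | 27% | about 29–30 points |
| 0.05 | 16% | about 32–34 points |
| 0.10 | 10% | about 37–39 points |

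Example: for pC = 40%, ICC 0.05 and d = 34.2 points, SE = √{(0.240 + 0.191)/1000 × 5.95} = 0.0507. Then 0.142/0.0507 = 2.80 and Φ(2.80 − 1.96) = 80%.

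**Step 5: does N = 2,000 reveal the intended null?** Against zero, a true 20 points at ICC 0.10 gives 79–81% power for pC of 30–50%. Against the margin, a true 30 points at ICC 0.02 gives 78% at pC = 40%. The same N fits either null under some inputs, so it does not settle the question.

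The SE ignores the matched pairs and uses a normal approximation, so the figures in steps 4 and 5 are approximate. Step 2 depends on neither.

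**The case against.** The strongest defence is that the margin is deliberate. It appears in the primary outcome, in Table 2 and in the formal hypotheses, so the Sample size section is the outlier. Requiring uptake to exceed control by a policy-relevant amount is a legitimate design, and the assumed effect above the margin may be in the full protocol or the SAP. This stands as to intent: the article does not show which null was meant. It does not rescue the power statement. The words at least make 20 points the smallest difference claimed to be detectable, and an unseen document cannot make both printed nulls true.

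Three stronger readings are tempting, and the article does not support them.

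- **That 2,000 fits only a no-difference null, so the margin must be a slip.** Step 5 shows that it also fits the margin with a larger assumed effect.
- **That the cited HIV evidence predicts failure.** The Background says that secondary distribution of self-tests "substantially increased testing coverage (by 21%) among absent individuals or those who declined to participate". It does not say whether this is relative or in percentage points, nor whether it is a between-arm difference, so it cannot be placed on this trial's scale.
- **That a real benefit would be hidden.** The plan reports the difference with its confidence interval, and the odds ratio with its interval, so a lower limit above zero would be visible. Missing the margin would mean that an excess over 20 points was not shown. The primary hypothesis would still have failed on its own terms.

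**Conclusion.** The point holds as a contradiction between sections and as a wrong power statement. For the test in Statistical methods, power at a true 20 points is 2.5%, not 80%. That follows from the one-sided alpha alone and rests on no assumed input, although with 20 clusters the actual rate may drift slightly, as in the simulation. The true difference needed for 80% power against the margin is about 25 to 39 points, depending on an assumed ICC of 0 to 0.10 and control uptake of 10–50%. No single replacement figure can be given from the article. N = 2,000 is not shown to be wrong, and the absence of ICC and control uptake from an article is not itself the fault. Because this is the confirmatory test, it has to be settled before analysis.

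**What to change.** State one primary null in Outcomes, Sample size, Table 2 and the hypotheses under Statistical methods, by a dated amendment made before outcome data are examined. There are two ways.

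(a) Test H0: pI − pC ≤ 0 against > 0 at one-sided 0.025. This agrees with the Sample size section and with the aim of showing increased uptake. Keep 20 points as the planning difference and as a benchmark for reading the confidence interval, and take the margin out of the other three places.

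(b) Keep the 20-point margin. Replace the null and the power statement in Sample size with the true difference above 20 points, the ICC and the control uptake for which 80% power is claimed.

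Neither option needs more participants. Under (a), a claim of superiority by more than 20 points becomes descriptive. It also replaces the null with an easier one in an unblinded trial whose enrolment began in November 2021, so the amendment must record its timing relative to any access to outcome data. Under (b), the 80% is tied openly to a larger effect, which the sponsor must be able to justify.

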**Methods:**

This is a parallel group, non-blinded, cluster randomised trial comparing secondary distribution of HCV self-testing with secondary distribution of information pamphlets encouraging individuals to visit a testing facility for HCV screening. The cluster allocation ratio is 1:1. Clusters will be randomised either to HCV self-testing distributed via study staff or control clusters where information on HCV will be given and the participant will be requested to attend their local hospital for HCV screening. In both clusters, only households with a member who has not yet been screened as part of the larger micro-elimination project will be included. The primary outcome is the number and proportion of participants who report completion of testing. Secondary outcomes include the number and proportion of participants who a) receive a positive result and are made aware of their status, b) are referred to and complete HCV RNA confirmatory testing, and c) start treatment. Acceptability, feasibility, attitudes towards HCV testing, and cost will also be evaluated. The target sample size is 2,000 participants.

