#### Assignment of interventions: allocation

Each member (neighbourhood block) of a matched cluster pair will be randomly allocated to the intervention or control group using a simple, computer-generated randomisation list. Each matched pair will be established based on similarities in type of geography (urban/peri-urban or rural), population size, sex distribution, age range, income and literacy. Within each UC and type of cluster (rural versus peri-urban), clusters will be put into pairs based on average household size (i.e. total estimated population in the cluster divided by the number of structures in the cluster). For example, the two rural clusters with the two largest average household sizes will be paired, followed by the next two rural clusters with the third and fourth largest average household sizes, and so on. Similar pairing will be performed for peri-urban clusters. If there are more than two clusters with the same average household size, then the estimated average age will be used as a tiebreaker, and pairs will be selected based on the closest estimated average age in those clusters. Once all clusters have been put into pairs, each member of a pair will be randomised to the intervention or control group.

For the face-to-face interviews, a subset of the main participants will be selected. Based on the study cluster assignment and testing results, study participants will be divided into the following eight subgroups:

Intervention group:In a rural cluster in the intervention group and completed a testIn a rural cluster in the intervention group, but did not complete a testIn a peri-urban cluster in the intervention group and completed a testIn a peri-urban cluster in the intervention group, but did not complete a test

Control group:In a rural cluster in the control group and completed a testIn a rural cluster in the control group, but did not complete a testIn a peri-urban cluster in the control group and completed a testIn a peri-urban cluster in the control group, but did not complete a test

For each subgroup, a randomly ordered list of participants will be generated via computerised randomisation. Then, for each subgroup, participants will be contacted by study staff in descending order on the list until a maximum of 15 individuals in each subgroup have completed the survey.

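### The primary model has a random effect for the matched pair but none for the randomised cluster, so the lower limit compared with the 20-point margin is too high

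*Protocol article*

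**What the plan says.** **Randomisation.** Protocol article, Assignment of interventions: allocation: "Each member (neighbourhood block) of a matched cluster pair will be randomly allocated to the intervention or control group". Each pair therefore contains one self-test block and one pamphlet block. The abstract's Methods paragraph adds: "The cluster allocation ratio is 1:1".

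**Size.** Sample size section: "There will be up to 20 clusters, each comprising up to 150 to 200 households", and "A minimum of 2,000 participants who meet the inclusion criteria will be enrolled in the study". With all 20 clusters there are 10 pairs.

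**Primary analysis.** Statistical methods section: the difference and its interval are to be "estimated using a generalised binary mixed logit model with “cluster pair” as a random effect and “group” as a fixed effect". The decision rule follows from three further statements:
- "The difference pfo,I—pfo,C will be assessed using a one-sided test with a margin of 20" percentage points;
- "The alpha level for the analysis will be set at 0.025 (1 one-sided test with an alpha level of 0.025";
- "The two-sided 95% asymptotic confidence interval will be used to derive the one-sided lower 97.5% confidence limit", and that limit is the one used for interpretation.

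No term for cluster, pair-by-group term, robust variance or small-sample correction is stated. Table 2 names only a comparison of proportions for this endpoint. No ICC appears anywhere in the article.

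**The concern.** The model accounts for the wrong level. A random intercept for the pair describes how one pair differs from another. Both arms of a pair share it, so it drops out of the comparison between them. What remains is treatment plus every other difference between the two blocks. In this design that block-to-block difference is the randomisation error of the treatment contrast, and the model sets its variance to zero. Participants are then treated as independent within a pair, as if they had been randomised one by one.

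The primary conclusion turns on whether a lower confidence limit clears 20 points, so an understated standard error acts directly on it.

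**Working it through.** **The plan's own figure.** The minimum of 2,000 cannot be reproduced from the stated inputs (80% power, alpha 0.05, 20-point difference), because neither a control rate nor an ICC is given. With no clustering and control rates from 5% to 70%, a two-sided test of two proportions needs 98 to 194 people in total. If all of the excess were an allowance for clustering, the implied design effect would be about 10 to 20. The document does not say so, and I draw no ICC from it.

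**Inputs for the check.**
- From the Sample size section: 20 clusters, hence K = 10 pairs, and m = 2,000/20 = 100 per cluster, taking sizes as equal.
- From Statistical methods: nominal one-sided error 0.025.
- Assumed: ρ, the ICC between members of a block that remains within pairs after matching, from 0.001 to 0.05.

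**Formulae.**
- Variance implied by the pair-only model, with p_I and p_C the uptake in each arm: [p_I(1−p_I) + p_C(1−p_C)]/(Km).
- True variance: the same, multiplied by DE = 1 + (m−1)ρ = 1 + 99ρ.
- The standard error is too small by √DE. The true one-sided error at the boundary is 1 − Φ(1.96/√DE).

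| Assumed ρ | DE | √DE | True one-sided error | Multiple of 0.025 |
|---|---|---|---|---|
| 0.001 | 1.10 | 1.05 | 0.031 | 1.2 |
| 0.005 | 1.50 | 1.22 | 0.055 | 2.2 |
| 0.01 | 1.99 | 1.41 | 0.082 | 3.3 |
| 0.02 | 2.98 | 1.73 | 0.128 | 5.1 |
| 0.05 | 5.95 | 2.44 | 0.211 | 8.4 |

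The error doubles at ρ of about 0.004 and triples at about 0.009.

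**Check by simulation.** The pair-only random-intercept logit was fitted by quadrature to 10 pairs of blocks of 100, with a control rate of 30% and a true difference of exactly 20 points (600 runs per setting, with and without extra between-pair variation). The proportion of runs in which the lower limit exceeded 20 points was:
- ρ = 0: 0.025 to 0.030
- ρ = 0.005: 0.047 to 0.055
- ρ = 0.01: 0.078 to 0.092
- ρ = 0.02: 0.132 to 0.150
- ρ = 0.05: 0.215 to 0.223

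The correct result at ρ = 0 shows that the missing cluster variance causes the inflation, not the fitting. On the same data, a t-interval with 9 degrees of freedom on the ten within-pair differences gave 0.017 to 0.033, which is nominal within simulation error.

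**What it does to one result.** Suppose uptake is 30% and 55%, a difference of 25 points.
- Pair-only: SE = √[(0.30×0.70 + 0.55×0.45)/1,000] = 2.14 points. Lower limit 25 − 1.96×2.14 = 20.8, so the margin is met.
- With ρ = 0.02 and t on 9 df: SE = 2.14×1.73 = 3.69 points. Lower limit 25 − 2.262×3.69 = 16.6, so the margin is not met.

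**The case against.** **The size is not known.** This stands. A reader might infer that type I error is certain to be inflated several-fold. The document gives no ICC, and the relevant one is what remains after pairing within area type on average household size. At 0.001 the inflation is only 1.2-fold; a three-fold inflation needs about 0.009 or more. A residual ICC above zero is nevertheless plausible. The Limitations section expects control uptake to depend on distance to the hospital, and distance is not among the listed matching factors. Several absent members of one household can also be enrolled.

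**The test is against a margin.** This also stands. A reader might infer that the model would turn chance differences between blocks into an effect where none exists. The lower limit used for interpretation is compared with 20 points, so that is very unlikely. At 50% uptake in both arms the naive SE is √(0.5/1,000) = 2.24 points, and the observed difference must exceed 20 + 1.96×2.24 = 24.4 points. With a true effect of zero and ρ = 0.05 the real SE is 5.45 points and the chance is about 4 in a million; at ρ = 0.10 it is about 0.0005. The Sample size section does also state a null of no difference. The same model tested against zero would be inflated to a similar degree, but that is not the test tied to this interval.

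**The separate SAP may repair it.** This is weak. The article states the primary model itself, so the point is a rule that is wrong as written, not a detail left out.

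**Matching deals with clustering.** It reduces the residual variation between blocks. It does not make it zero, as this model assumes.

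**Conclusion.** The point holds. That the variance omits the randomised unit follows from the text alone, and no other section corrects it. The lower 97.5% limit is too high whenever the residual within-pair ICC is above zero.

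The size is conditional on equal clusters of about 100 and on the assumed ICC. Over 0.001 to 0.05, standard errors are too small by a factor of about 1.05 to 2.4, and the one-sided error at the 20-point boundary is about 0.03 to 0.21 in place of 0.025. Spreading 2,000 people over fewer than 20 clusters, which the plan allows, raises m and with it the inflation. So do unequal cluster sizes.

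The harm is a false claim that self-testing raises uptake by more than 20 points. It should be settled before the primary analysis, because the same data can pass or fail the margin depending on this term.

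**What to change.** **Primary comparison.** Base the variance on the randomised cluster, in one of two ways:
1. *Preferred.* Keep the logit mixed model with group as fixed effect, and add a random effect for cluster nested in pair with a small-sample degrees-of-freedom correction. Derive the risk difference and its lower limit from this model.
2. *Alternative.* Use a t-interval on the within-pair differences in cluster proportions, with degrees of freedom equal to the number of pairs minus one (9 only if all 20 clusters are used). State the weighting. The plan defines uptake over individuals, and the two union councils have about 10,000 and 50,000 people, each split into ten blocks. Equal weights could therefore shift the estimand.

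In either case compare the lower limit with the 20-point margin, and bring Table 2 into line.

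**Secondary endpoints.** Do not carry this structure over automatically. If the 5% population figure applied and everyone tested, there would be 100 antibody-positive people, or about five per cluster, and some control clusters might have none. Report these descriptively, or with cluster-robust methods where they can be estimated.

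**Cost.** A sentence or two in the protocol and SAP, and no new data. Intervals become wider, by √DE before the t correction, and power against the margin is lower than the current model implies. The sample size justification should acknowledge this.
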